#### Main trial sample size calculations

2.4.3

The sample size calculation is based on a difference in the proportion of people with intellectual disability making an informed decision about cervical screening pre-and-post the intervention (53). Noting that making an informed decision may not necessarily lead to a person having a screening test due to barriers such as a history of sexual assault, a baseline proportion of 20% was selected based on the last published national Australian figure of 10% screening uptake for this group (26). It was estimated that 44 participants would be needed to detect a change in the proportion (%) of those assessed as being able to make an informed decision (across the domains of knowledge, attitudes, and intention to screen) from 20% pre-intervention to 50% post-intervention, with power and alpha set at 80 and 5%, respectively. Due to the novelty of our study in terms of participants and intervention, no known estimates were available for pre-post correlation between the items in the modified informed decision-making tool or outcome variability at both time points. Consequently, a conservative approach was adopted by assuming there was zero correlation between pre-post observations measured by the modified tool and that these observations displayed maximum variability, i.e., standard deviation = 0.5 (54). Assuming a dropout rate of 10%, the adjusted sample was increased to 48.

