#### Sub-study sample size considerations

2.4.7

Sub-study sample size calculations are based on a difference in the pre-post intervention survey outcomes (57). Given the lack of baseline data related to sub-study outcomes related to health literacy, attitudes and self-efficacy for families and support people, the sample size (*n* = 48) derived for the main trial was also considered to be adequate to detect a change of 30% in pre and post measures for this group. For healthcare providers, it was estimated that a sample size of 393 would be needed to detect a change in preparedness to provide cervical screening from 65% pre-intervention to 75% post-intervention based on a recent Australian cervical screening survey (56). As per the other sample size calculations, a conservative approach was undertaken. Assuming a dropout rate of 10%, recruitment of 433 healthcare providers would be required (54).

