#### Data analysis

2.5.2

Qualitative data collection and thematic analysis will follow the principles and processes described earlier. Descriptive statistics will summarise participants’ baseline characteristics in the main trial and sub-studies. The impact of the intervention (i.e., effects) on the primary and secondary outcomes will be assessed using multivariable logistic regression modelling. This approach adjusts for the data being correlated because of the pre-and-post study design. Effects will be reported as adjusted odds ratios (ORs) with 95% Confidence Intervals (CIs). Univariable logistic analyses will be used to identify potentially confounding variables such as age and place of residence. Two-sided *p*-values less than 0.05 will be considered as significant. Stata Version 18 (StataCorp LLC, College Station, TX) will be used to analyse data.

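### The 10% dropout allowance is slightly miscalculated: 48 and 433 recruits leave about 43 and 390 completers, just under the stated 44 and 393

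*Protocol article*

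**What the plan says.** Section 2.4.3 of the protocol article (Main trial sample size calculations) bases the main trial on a rise in the proportion making an informed decision "from 20% pre-intervention to 50% post-intervention", "with power and alpha set at 80 and 5%, respectively". It takes a deliberately cautious variance, "assuming there was zero correlation between pre-post observations" and "standard deviation = 0.5" at both time points. The result is stated as a requirement: "It was estimated that 44 participants would be needed to detect a change in the proportion". The allowance for loss follows: "Assuming a dropout rate of 10%, the adjusted sample was increased to 48".

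Section 2.4.7 (Sub-study sample size considerations) does the same for healthcare providers. It needs 393 to detect a change from 65% to 75%, says that the same conservative approach was taken, and concludes: "Assuming a dropout rate of 10%, recruitment of 433 healthcare providers would be required". It does not restate power or alpha for this group. For families and support people it reuses the main trial's 48 with no separate calculation.

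Neither section gives the inflation formula. The 48 also stands in the Abstract and in sections 2.4.2 and 2.4.5, and the 433 in the Abstract and section 2.4.6.

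**The concern.** A dropout allowance exists so that the required number remains after the assumed loss. If a fraction d is lost, recruitment must be n/(1 − d). Multiplying by (1 + d) always gives too few, because the loss falls on the larger recruited number. Both stated targets fail this simple check: taking 10% off them does not return the number that the same paragraph says is needed.

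What is at stake is the internal consistency of the headline sample sizes and a small loss of power. The Ethics statement says that Stage 2 is still to be registered, so the figures can be put right before they are entered there.

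**Working it through.** **Inputs.** Main trial (section 2.4.3): difference d = 0.50 − 0.20 = 0.30, SD 0.5 at each time point, pre-post correlation 0, power 80%, alpha 5%. The two-sided reading comes from section 2.5.2 (Data analysis): "Two-sided *p*-values less than 0.05 will be considered as significant". Providers (section 2.4.7): d = 0.75 − 0.65 = 0.10. SD, correlation, power and alpha are assumed to be as in the main trial, because the section refers back to the other calculations. Dropout is 10% in both.

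**Step 1: reproduce the plan's required numbers.** The normal approximation for a paired difference is n = 2 × SD² × (1 − correlation) × (z0.975 + z0.80)² / d².
- Main trial: 0.5 × (1.960 + 0.8416)² / 0.09 = 43.60, so 44. This matches.
- Providers: 0.5 × (1.960 + 0.8416)² / 0.01 = 392.44, so 393. This matches.

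Both figures come out exactly, which supports the assumed provider inputs. A one-sided test would give 35 and 310, so the two-sided reading is the right one. The fault is confined to the inflation step.

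**Step 2: apply the stated dropout to the stated targets.**
- 48 × 0.9 = 43.2, about 43, against 44.
- 433 × 0.9 = 389.7, about 390, against 393.

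**Step 3: look for the rule that was used.**

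| Rule | Main trial | Providers |
|---|---|---|
| Stated in the article | 48 | 433 |
| Required n × 1.1 | 48.4 | 432.3 |
| Unrounded n × 1.1 | 47.96 | 431.7 |
| Required n / 0.9 | 48.9 | 436.7 |
| Unrounded n / 0.9 | 48.45 | 436.05 |

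The best match is the required number × 1.1, but then 48.4 was rounded down and 432.3 was rounded up. None of these rules, with one rounding convention, gives both 48 and 433. Dividing by 0.9 and rounding up gives 49 and 437.

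**Step 4: the effect on power.** With the same formula, power = Φ(d / √(0.5/n) − 1.960).
- Main trial: 80.4% at 44 and 79.4% at 43.
- Providers: 80.1% at 393, 79.8% at 390 and 79.7% at 389.

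**Step 5: how much dropout the stated targets do tolerate.**
- 1 − 44/48 = 8.3%.
- 1 − 393/433 = 9.2%.

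**Step 6: how conservative the variance is.** The plan's own proportions imply less variance than SD 0.5 at both time points. A McNemar-type calculation with independent pre and post responses has discordant proportions 0.40 and 0.10 for 20% to 50%, and 0.2625 and 0.1625 for 65% to 75%. It needs 42 and 332 participants. Power is about 82% at 43 and about 86% at 389 or 390. If SD 0.5 is kept and the correlation is 0.05 in place of 0, power is 81.4% at 43 and 81.6% at 389.

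**The case against.** The strongest reply is that this is rounding. The gap is 1 participant in the main trial and 4 of 437 providers (0.9%). The unrounded main-trial requirement divided by 0.9 is 48.45, which rounds to 48. The 10% is itself a round guess. The outcome is asked at the start of a workshop and again at its end or within a week, which leaves limited room for loss. Section 2.4.2 also calls the main trial a pilot for a larger, adequately powered study. Most of this stands, and it fixes the weight of the point. It does not make the step correct: the article states 44 and not 43.60, required sample sizes are rounded up, and the same route gives 436 or 437 for providers, never 433.

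A reader might infer that the trial is underpowered. The documents do not support that. The shortfall is about half a point under a variance chosen as a safety margin, and power exceeds 80% under the plan's own proportions. Substituting a paired t-test gives 77.6% at 43, which looks worse. But that test gives only 78.6% at the full 44, so most of the drop comes from changing the test and only about 1 point from the inflation.

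A reader might also infer that all three recruitment targets miss a stated 80% power. That goes too far. Only the main trial states 80%. For providers it is implied by the reference to the other calculations. For families and support people, section 2.4.7 gives no power or dropout calculation and simply judges 48 adequate.

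**Conclusion.** The point holds as a minor arithmetic correction. At the stated 10% dropout, the targets of 48 and 433 leave about 43 and 390 completers, short of the stated requirements by about 1 participant and 3 to 4 providers. By the plan's own conservative formula the cost is power of about 79.4% and about 79.7%. The provider figure assumes that SD 0.5, zero correlation, 80% power and two-sided 5% carry over from the main trial, an assumption supported by the exact reproduction of 393. Nothing in the design, conduct or analysis has to change, and no conclusion about material underpowering follows.

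**What to change.** Choose one of two routes, and state the inflation formula in sections 2.4.3 and 2.4.7.

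1. Keep 48 and 433, and restate them as about 43 and 390 completers at 10% dropout with power just under 80%, or as tolerating about 8% and 9% dropout. This changes only the wording.
2. Divide by 0.9 and round up, giving 49 and 437 in the Abstract and in every section of 2.4 where the figures appear. This costs 1 more participant and 4 more providers. The 5 or 6 workshops of about 10 people planned in section 2.4.2 already have room for 49.

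Under either route, the 48 for families and support people should follow the main-trial figure, since it is borrowed from there. Make the change before Stage 2 is registered, so that the registry and the article agree.

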#### Data linkage

2.4.4

To determine participants’ screening histories and participation in the NCSP in the subsequent 9-months after the trial, linked cervical screening data within the NCSR records, held by the Cancer Institute NSW, will be accessed, and managed according to mandated data security measures (55). These data will also allow determination of whether the most recent cervical screening test (if any) since the trial was self-collected or collected by a clinician.

#### Sub-study participants and study design – families and support people

2.4.5

Family members and support people of people with intellectual disability will be recruited into a single-arm sub-study (*n* = 48; see Table 3 for eligibility criteria). Over a 4-month timeframe this group will receive the co-produced accessible cervical screening resource and accompanying supporting materials about how it can be used to support people with intellectual disability to undertake cervical screening (the intervention). These resources will be housed on the ScreenEQUAL website, and their use will be tracked by fit-for-purpose methods including Google Analytics. Participants will be invited to complete pre-post surveys delivered online, by mail, or in-person, depending on their preference. A subset of participants (*n* ≈ 20 or until saturation is reached) will be invited to join post-intervention qualitative interviews. The surveys and interview domains will be informed by existing surveys, Stage 1 outputs and the Advisory Group, and will be piloted by family members and support people prior to the trial.

#### Sub-study participants and study design – healthcare providers

2.4.6

Healthcare providers, who offer services for people with intellectual disability will be recruited into a single-arm sub-study (*n* = 433; see Table 3 for eligibility criteria). Over a 4-month timeframe, this group will receive the online training materials aimed at supporting delivery of trauma-informed cervical screening care for people with intellectual disability. Training uptake and engagement will be tracked using fit-for-purpose approaches. Participants will be invited to complete online pre-post surveys and a subset of participants (*n* ≈ 20 or until saturation is reached) will be invited to participate in post-intervention qualitative interviews. The surveys and interview domains will be informed by an existing healthcare provider survey (56), Stage 1 findings, and the Advisory Group, and will be piloted by healthcare providers prior to the trial.

#### Sub-study sample size considerations

2.4.7

Sub-study sample size calculations are based on a difference in the pre-post intervention survey outcomes (57). Given the lack of baseline data related to sub-study outcomes related to health literacy, attitudes and self-efficacy for families and support people, the sample size (*n* = 48) derived for the main trial was also considered to be adequate to detect a change of 30% in pre and post measures for this group. For healthcare providers, it was estimated that a sample size of 393 would be needed to detect a change in preparedness to provide cervical screening from 65% pre-intervention to 75% post-intervention based on a recent Australian cervical screening survey (56). As per the other sample size calculations, a conservative approach was undertaken. Assuming a dropout rate of 10%, recruitment of 433 healthcare providers would be required (54).

### Outcome measures and data analysis

2.5

#### Outcome measures

2.5.1

The study outcome measures align with the study aims. Triangulation of quantitative and qualitative outcome measures will be used to evaluate pre-post differences for the main trial and sub-studies. The qualitative outputs will provide insights into participants’ perceptions of the resources and facilitate the interpretation and explanation of the primary and secondary outcomes.

The primary outcome measure is informed decision-making about cervical screening by people with intellectual disability across the domains of knowledge, attitudes to screening and intention to screen, measured by an accessible modified tool (49–52). The modified tool will collect data during accessible workshops in the main trial as described in section 2.4.2. Given the lack of an existing validated tool to measure informed decision-making by people with intellectual disability about health screening, the research team led by the chief investigator with intellectual disability and health literacy experts, aims to modify an existing tool (49, 50). The tool will likely be employed using interviews to assess knowledge, attitudes and intention to screen including open-ended accessible questions around the role of screening in preventing cervical cancer, screening options, including the choice of a self-collected test, and the likely consequences of screening including recommended follow-up after an abnormal test result. Similarly, participants’ attitudes towards screening may include agreement or disagreement with accessible statements that cervical screening is ‘beneficial’ or ‘harmful,’ while intention to screen may be assessed through an accessible scale with responses ‘I will,’ ‘I am not sure,’ ‘I will not.’

Secondary outcome measures (assessed during the main trial sub-studies) are:

participation in the NCSP by people with intellectual disability, including uptake of self-collection versus clinician collection;pre-post differences in family members’ and support peoples’ health literacy, attitudes, and self-efficacy in supporting cervical screening for people with intellectual disability;pre-post differences in healthcare providers’ knowledge, attitudes, self-efficacy and preparedness in supporting and providing cervical screening for people with intellectual disability.

The acceptability, feasibility and usability of the co-produced information resources and training materials for families and support people and healthcare providers will also be assessed through post-intervention surveys and the qualitative interviews, supplemented by data tracking of engagement by families and support people and healthcare providers with the resources and training materials on the ScreenEQUAL website. Final adjustments to the resources and training materials required as a result of the trial outcomes will be made at the conclusion of the study.

#### Data analysis

2.5.2

Qualitative data collection and thematic analysis will follow the principles and processes described earlier. Descriptive statistics will summarise participants’ baseline characteristics in the main trial and sub-studies. The impact of the intervention (i.e., effects) on the primary and secondary outcomes will be assessed using multivariable logistic regression modelling. This approach adjusts for the data being correlated because of the pre-and-post study design. Effects will be reported as adjusted odds ratios (ORs) with 95% Confidence Intervals (CIs). Univariable logistic analyses will be used to identify potentially confounding variables such as age and place of residence. Two-sided *p*-values less than 0.05 will be considered as significant. Stata Version 18 (StataCorp LLC, College Station, TX) will be used to analyse data.

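### Logistic regression with odds ratios is fixed for every outcome, so any survey score in the sub-studies would most naturally be cut to yes/no, losing power for changes smaller than planned

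*Protocol article*

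**What the plan says.** Section 2.5.2 (Data analysis) of the protocol article names one model for everything: "The impact of the intervention (i.e., effects) on the primary and secondary outcomes will be assessed using multivariable logistic regression modelling". It names one effect measure: "Effects will be reported as adjusted odds ratios (ORs) with 95% Confidence Intervals (CIs". The test criterion is "Two-sided *p*-values less than 0.05 will be considered as significant". No model for a score or a mean appears.

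Section 2.5.1 (Outcome measures) lists as secondary outcomes the pre-post differences in family members' and support people's "health literacy, attitudes, and self-efficacy in supporting cervical screening for people with intellectual disability". For healthcare providers it lists knowledge, attitudes, self-efficacy and preparedness. No scale, scoring rule or cut-off is given for any of these, and sections 2.4.5 and 2.4.6 say the surveys are still to be developed and piloted.

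Sizing is on proportions. The main trial assumes a change "from 20% pre-intervention to 50% post-intervention", "with power and alpha set at 80 and 5%, respectively". Section 2.4.7 carries the resulting 48 over to families and support people, where it "was also considered to be adequate to detect a change of 30% in pre and post measures for this group". Providers are sized on preparedness rising from 65% to 75%.

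**The concern.** Health literacy, attitudes, self-efficacy and knowledge are normally captured with several graded items or a total score. Ordinary logistic regression needs a two-category outcome, so under the stated model the natural route for such a measure is to split it at a threshold. A split ignores change within each category, makes the result depend on where the threshold falls, and usually lowers power. The family and support sub-study, with about 43 completers, has least room for this: a real but moderate improvement in scores could be reported as non-significant. The model was fixed before the instruments were known, so the wording would apply to whatever scale is eventually chosen.

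**Working it through.** **1. The plan's own figures.** Inputs from section 2.4.3: SD 0.5 at each time, correlation 0, two-sided alpha 5%, power 80%. The SD of the paired difference is √(0.25 + 0.25) = 0.707.

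- Difference 0.30: n = [(1.960 + 0.842) × 0.707 / 0.30]² = 43.6, so 44, as stated.
- Difference 0.10 (65% to 75%): n = 392.4, so 393, as stated.

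Both are yes/no comparisons. With 10% dropout, 48 × 0.9 = 43.2, so about 43 completers.

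**2. Assumptions for the comparison.** The documents give no score distribution, so these are assumed: a normal score with unit SD at both times, pre-post correlation ρ from 0 to 0.7, and an improvement of 0.45 SD. Two cuts are tried: one at the baseline median, one leaving 20% positive at baseline. A 0.45 SD shift then moves 50% to 67%, or 20% to 35%, which is 15 to 17 points, about half the planned 30.

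**3. Formulas.**

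- Score: paired t-test on 42 df with non-centrality 0.45 × √43 / √(2(1 − ρ)). At ρ = 0.5 this is 2.95, giving 82% power.
- Cut: McNemar's test, standing in for the paired logistic model. With b and c the probabilities of changing to yes and to no, d = b − c and ψ = b + c, approximate power is Φ[(d√n − 1.96√ψ) / √(ψ − d²)]. At ρ = 0.5 with the median cut, b = 0.262 and c = 0.089, so d = 0.174, ψ = 0.351 and power is 48%. Summing over the binomial outcomes gives 49%.

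**4. Power at 0.45 SD, n = 43** (cut columns by binomial summation):

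| ρ | Score | Median cut | 20% positive at baseline |
|---|---|---|---|
| 0 | 53% | 38% | 33% |
| 0.3 | 68% | 44% | 38% |
| 0.5 | 82% | 49% | 42% |
| 0.7 | 96% | 58% | 51% |

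Simulation of the same set-up agrees to within about one point (54% and 34% at the lower ends). A coarser measure narrows the gap without closing it: a single five-level item, scored, has about 75% power at ρ = 0.5.

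**5. Power at the planned change.** Moving from 20% to 50% is a 0.84 SD shift on this scale. With n = 43, the formula in step 3 gives the yes/no analysis 82% (ρ = 0) to 95% (ρ = 0.7), and binomial summation gives 85% to 98%. The score analysis has 97% or more. For providers at 65% to 75% with n = 393, the yes/no analysis has 86% to 99%.

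**The case against.** The strongest reply is that the plan is coherent on its own terms: the outcomes it quantifies are proportions, the sample sizes reproduce as yes/no comparisons, and logistic regression follows. The surveys are not written, so graded scores are an inference from the constructs, and scoring rules are commonly left to a fuller document. All of this stands, and it makes the point conditional. It does not remove it, because the article goes beyond leaving the model open: it names one model and one effect measure for every outcome.

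Three stronger readings are tempting and are not supported.

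- A reader might infer that the plan forces dichotomising. Ordinal logistic regression also yields odds ratios and is not excluded, although it is not named.
- A reader might infer that the family and support sub-study misses its 80% power. It was sized for a 30-point change and keeps that power. The loss is relative to a score analysis and affects smaller changes.
- A reader might infer that the intention item needs its own ordinal test, since "intention to screen may be assessed through an accessible scale with responses" at three levels. That is only a possible component of the primary outcome, which is sized as the proportion able to make an informed decision. For that outcome logistic regression is suitable.

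**Conclusion.** The point holds in a limited, conditional form. The stated model fits informed decision-making (yes/no), screening uptake and provider preparedness. It is a poor default for health literacy, attitudes, self-efficacy and knowledge if these are measured as scores. In that case, with 43 completers, power for a 0.45 SD improvement is about 33% to 58% after a cut, against about 53% to 96% on the score. These figures rest on an assumed normal score, correlations of 0 to 0.7, two illustrative cuts, and McNemar's test in place of the adjusted model. No stated sample size or power is wrong. Smaller changes still matter for families and support people, because section 2.4.7 acknowledges that baseline data are lacking, so the 30-point change is borrowed from the main trial.

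**What to change.** Amend section 2.5.2 as follows.

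- Use logistic regression, allowing for the pre-post pairing where there is one, for binary outcomes: informed decision yes/no, screening uptake, and provider preparedness as sized (65% to 75%).
- Analyse survey scores on their own scale: mean paired change with a 95% CI, or a linear mixed or ordinal model with a term for time.
- Keep any dichotomised version of a score as a supplement, with its cut-off fixed before the data are seen.

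No separate test of the intention item is needed. The change uses the same data and the same numbers of participants, and can be made while the Stage 2 surveys are being finalised. At the planned change, 43 completers give a score analysis at least 97% power under the assumptions above, so the sample size of 48 need not change. The cost is that results appear on more than one effect scale.

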#### Main trial design

2.4.2

The main trial is a single-arm study aimed at evaluating the primary study outcome (a change in informed decision-making about cervical screening by people with intellectual disability). An accessible informed decision-making tool will be created based on existing tools and surveys informed by the research team, Advisory Group members with intellectual disability and experts in health literacy. The modified tool will collect data via interviews using a brief set of pre-intervention open-ended accessible questions across three domains: knowledge, attitudes to screening and intention to screen (49–52). The trial will serve as a pilot study for a larger appropriately powered validation trial.

People with intellectual disability (*n* = 48) will be invited to join one of 5 or 6 accessible workshops of approximately 10 people with intellectual disability and 2 to 3 trained support people, facilitated by members of the research team. The workshops will last approximately 2 to 3 h. Support people will be identified through Family Planning Australia networks to participate in a pre-workshop session where they will receive training according to a structured session plan on how to use the co-produced resource with people with intellectual disability. The trained support people will then use the resource with workshop participants in a way that simulates what would happen in a community setting (the intervention). Individual participants with intellectual disability will be supported to complete a brief set of pre-intervention open-ended accessible questions to assess informed decision making at the start of the workshop which will be repeated at the end of the workshop or within the next week depending on the participant’s choice. Qualitative data regarding the overall perceptions of the co-produced resource will be gathered during the workshops by the research team through audio-recording of the group discussion.

A subset of participants with intellectual disability (*n* ≈ 20 or until saturation is reached) will be invited to participate in post-intervention qualitative interviews, with the option of additional body-mapping, to provide further insights into perceptions of the resources and to support the interpretation of the study outcomes (41).

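### The Data analysis section credits multivariable logistic regression with handling the pre-post pairing, which the model as named does not do; a correlated-data method should be named

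*Protocol article*

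**What the plan says.** Under Data analysis (2.5.2), the intervention's effect on the primary and secondary outcomes "will be assessed using multivariable logistic regression modelling". The next sentence gives the reason: "This approach adjusts for the data being correlated because of the pre-and-post study design". Results are to be adjusted odds ratios with 95% confidence intervals, and two-sided p-"values less than 0.05 will be considered as significant". Covariates are chosen by a screen: "Univariable logistic analyses will be used to identify potentially confounding variables such as age and place of residence".

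The data are paired. Under Main trial design (2.4.2), each participant answers the same questions "at the start of the workshop which will be repeated at the end of the workshop or within the next week". The sample size section (2.4.3) plans for a change "from 20% pre-intervention to 50% post-intervention, with power and alpha set at 80 and 5%, respectively" and assumes zero pre-post correlation because no estimate was available.

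No section mentions generalised estimating equations (GEE), a participant random effect, conditional logistic regression, McNemar's test or cluster-robust standard errors.

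**The concern.** Multivariable means that there are several covariates. It does not describe how repeated records on one person are handled. Ordinary logistic regression on stacked pre and post records assumes that all records are independent given the covariates, and adding age or residence does not remove the dependence between two answers from the same person. The article therefore states a property that the named model lacks, which is more than leaving a detail to a later document. An analyst who followed the text literally would fit the ordinary model and believe the pairing had been dealt with.

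The covariate screen adds to the problem for the pre-post contrast. In the main trial the two measurements are at most about a week apart, so age and residence are the same at both. They cannot confound a within-person change. Adjusting for them mainly moves the odds ratio through non-collapsibility.

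At stake are the interval and p-value for the primary outcome and for the pre-post outcomes of both sub-studies.

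**Working it through.** **Inputs.** From the article: 20% to 50%, 44 evaluable participants, SD 0.5, zero correlation, two-sided 5%, 80% power; for healthcare providers 65% to 75% and 393. Assumed, because the article gives no value: pre-post correlation ρ from −0.2 to 0.5. With margins of 20% and 50%, the largest possible ρ is √[(0.2 × 0.5)/(0.8 × 0.5)] = 0.5, so the top of the range is a boundary case.

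**1. The plan's own figures.** n = (1.960 + 0.842)² × 2 × SD² × (1 − ρ)/δ².
- Main trial: 7.849 × 2 × 0.25/0.30² = 43.6, rounded up to 44.
- Providers: 7.849 × 2 × 0.25/0.10² = 392.4, rounded up to 393.

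Both reproduce. The sizing is for paired data with ρ set to zero.

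**2. Large-sample standard error of the pre-post log odds ratio (OR 4.0, 44 pairs).**
- Records treated as independent: 1/(44 × 0.16) + 1/(44 × 0.25) = 0.1420 + 0.0909 = 0.2330, SE 0.483, whatever ρ is.
- Allowing for pairing, subtract 2ρ/(44 × √(0.16 × 0.25)) = 0.2273ρ.

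| ρ | SE, ordinary | SE, paired | Ratio | 95% CI, ordinary | 95% CI, paired |
|---|---|---|---|---|---|
| 0 | 0.483 | 0.483 | 1.00 | 1.55–10.30 | 1.55–10.30 |
| 0.2 | 0.483 | 0.433 | 1.11 | 1.55–10.30 | 1.71–9.35 |
| 0.3 | 0.483 | 0.406 | 1.19 | 1.55–10.30 | 1.81–8.86 |
| 0.5 | 0.483 | 0.345 | 1.40 | 1.55–10.30 | 2.03–7.87 |

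**3. Simulation of the ordinary model, 44 pairs, 200,000 trials per setting.**

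| ρ | Type I error (20% v 20%) | CI coverage (20% to 50%) | Power (20% to 50%) |
|---|---|---|---|
| −0.2 | 6.6% | 92.7% | 83.7% |
| 0 | 4.4% | 95.0% | 85.6% |
| 0.2 | 2.4% | 97.2% | 88.3% |
| 0.3 | 1.6% | 98.1% | 89.8% |
| 0.5 | 0.5% | 99.4% | 93.6% |

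With pairing-aware standard errors, type I error is about 4.5% at zero and positive ρ. In these simulations the mean ordinary SE is 0.497, against an actual spread of the estimate of 0.433 (ρ 0.3) or 0.371 (ρ 0.5). The ratios are 1.15 and 1.34. They are smaller than the large-sample 1.19 and 1.40 because the log odds ratio varies more at n = 44 than the formula says. The 15% and 34% are the figures to use.

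**4. Power for other changes.**
- Main trial, 20% to 40%: ordinary model about 54%; McNemar about 67% (ρ 0.3) and 84% (ρ 0.5).
- Providers, planned 65% to 75%, n = 393: log OR 0.480, SE 0.157, and 0.480/0.157 − 1.96 = 1.10, so power is about 86% at ρ = 0 and higher at positive ρ.
- Providers, 65% to 71%: ordinary model 41% to 43%; paired methods 58% (ρ 0.3) and 72% (ρ 0.5).

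**5. Whether conditional logistic regression suits this sample.** It uses only discordant pairs. At 20% to 50% and ρ 0.3, the informed-to-uninformed cell has probability 0.20 − (0.10 + 0.3 × 0.20) = 0.04. It is empty in 0.96⁴⁴, about 17% of trials, and always at ρ 0.5. When it is empty, the conditional odds ratio is infinite.

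**The case against.** The strongest reply is that the sentence itself shows the authors recognised the pairing. GEE, random-intercept, conditional and cluster-robust logistic models are all logistic regressions available in Stata. A condensed article may leave the choice among them to a full protocol or analysis plan that is not shown. This stands as far as intent goes: the documents do not show that the team will run the wrong model. It does not rescue the sentence, which assigns the property to the model named.

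A reader might infer that every interval and p-value for the primary outcome will be wrong. The documents do not support that. At zero correlation, the article's own planning value, the ordinary model is valid. At positive correlation it errs towards caution and does not create false positives; only negative correlation would. The marked power losses are for changes smaller than those planned.

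A reader might also object that the trial is sized on a difference in proportions but reports an odds ratio. That is common practice and contradicts nothing in the article, so it is not counted here.

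On covariates, two points stand. Nine-month screening uptake is measured once, so age and residence are ordinary covariates there. With the 10% dropout that the plan expects, the mix of people can also differ between the two time points. The latter is a missing-data question, and univariable confounder screening is not the answer to it.

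The main trial is also described as a pilot for a larger validation trial, which limits the consequences.

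**Conclusion.** The concern holds in a limited form. The Data analysis section states that the named model accounts for pre-post correlation, and it does not. If it were run as named and responses were positively correlated, which is plausible for repeated answers from one person within about a week, the main-trial analysis would be conservative to the extent shown above: intervals too wide, tests too strict, and power lost mainly if the true change is smaller than planned. At the planned changes the power target of 80% is still met.

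The sizes rest on assumed correlations of 0.3 to 0.5 and on 44 complete pairs. That the sentence is wrong for the model as named rests on no assumption. It should be corrected before analysis because it governs the primary outcome.

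**What to change.** Replace the sentence in 2.5.2 with a named method for all pre-post outcomes. For example: logistic GEE with participant as the cluster and robust standard errors, the odds ratio being marginal, with McNemar's test and a paired difference in proportions (95% CI) as a simple companion. Conditional logistic regression is a poor default at n = 44, for the reason in step 5 of the working.

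State that age and residence will not be selected by univariable screening as confounders of the within-person contrast. They may stay as covariates for nine-month uptake.

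The cost is a few sentences of text. The methods are standard Stata commands, and neither new data nor a new sample size is needed.
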